### Sample size

Power calculations were conducted by means of the G*Power 3.1 software package [46]. According to pilot studies, an effect size of at least d = 1 can be assumed for the different paradigms and comparisons. For region of interest analysis with regions of 200 voxels, a sample of 30 per group should be sufficient to reach a power of 80% to detect differences at *p* < .05 (Bonferroni corrected for multiple tests). For the intervention study the same comorbid alcohol dependent and depressed participants will be randomly assigned to one of two group therapy interventions and asked to participate in a second fMRI session and follow up measurement. When assuming a small to medium effect size (*f* = .2) for the group x time interaction and a correlation among repeated measures of.7 (as typical for fMRI data), we achieve a power of 80% to detect differences at *p* < .05 (Boferroni corrected for a k = 200, region of interest) on the neural level even when we have to face a drop-out rate of 10%. While we expect an attrition rate of 20%, recruitment will be continued until the desired sample sizes are reached and drop-outs will be replaced by new participants.

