### Participants

Sixty comorbid alcohol dependent and depressed patients, 30 alcohol dependent only and 30 depressed only patients will be included for T1 assessment. Further, 30 healthy control participants (matched according to age, gender and educational level) will be recruited.

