### Primary outcome

In this study, neural activation and connectivity in the reward system and default mode network are the primary outcome measures. Neural correlates of reward and emotion processing in patients and healthy controls will be assessed by means of fMRI. While the first measurement will identify common and/or distinct neural signatures underlying the comorbidity of alcohol dependence and depression, the second measurement allows investigating the influence of the psychotherapeutic interventions on these target brain mechanisms.

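### The 80% power stated for the baseline comparisons with 30 per group does not follow from the plan's own inputs: per-voxel power is about 50% for 30 v 30 and 74% for 60 v 30 (two-sided)

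*Protocol article*

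**What the plan says.** The power statement for the baseline (T1) imaging comparisons is in the protocol article, Methods, Sample size. It gives these elements:

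- Effect size: "an effect size of at least d = 1 can be assumed for the different paradigms and comparisons".
- Region size: "For region of interest analysis with regions of 200 voxels".
- Claim: "a sample of 30 per group should be sufficient to reach a power of 80% to detect differences" at p < .05, with the qualifier "Bonferroni corrected for multiple tests".
- Software: "Power calculations were conducted by means of the G*Power 3.1 software package".

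The number of tests is not written into the baseline sentence itself. The intervention power statement in the same section does give it: "Boferroni corrected for a k = 200, region of interest".

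The Participants section sets the group sizes: "Sixty comorbid alcohol dependent and depressed patients, 30 alcohol dependent only and 30 depressed only patients will be included for T1 assessment", plus 30 healthy controls. The Aim section presents the baseline objective as comparing comorbid patients with the other three groups. The article does not name the group-level imaging test or say whether it is one- or two-sided.

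**The concern.** A Bonferroni factor of 200 is severe: it lowers the per-test alpha from .05 to .00025. With 30 per group and d = 1, the expected t statistic is just under 3.9, which is about where the critical value at that alpha lies. Power should therefore be near one half, not 80%.

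This matters because the sentence is the stated justification for 30 per group. The primary outcome is neural ("neural activation and connectivity in the reward system and default mode network are the primary outcome measures"), and the baseline scan is meant to separate signatures that the disorders share from those that differ. A non-significant difference could be taken as support for a shared signature. That inference is weaker at the true power than at the 80% that readers are told.

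**Working it through.** **Inputs**

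- d = 1, 30 per group, alpha .05 with Bonferroni correction, 200-voxel region, k = 200, stated power 80%: Sample size section.
- Comorbid 60, every other group 30: Participants section.
- Drop-out is not applied, because the Sample size section says that drop-outs are replaced.
- Assumption: two-sample t-test. Sidedness is not stated, so both versions are shown.

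**Formulas**

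- Per-test alpha = .05/200 = .00025.
- Noncentrality = d × √(n₁n₂/(n₁ + n₂)), with df = n₁ + n₂ − 2.
- Power = P(T > critical t), where T is noncentral t. The opposite tail is negligible here.

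**Attempt to reproduce the stated 80%: 30 v 30**

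- Noncentrality = 1 × √(900/60) = √15 = 3.873; df = 58.
- Two-sided: critical t = 3.903, power **49.5%**.
- One-sided: critical t = 3.688, power **57.6%**.

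**Comorbid group against a group of 30: 60 v 30**

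- Noncentrality = 1 × √(1800/90) = √20 = 4.472; df = 88.
- Two-sided: critical t = 3.818, power **73.9%**.
- One-sided: critical t = 3.615, power **79.9%**.

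**Other readings at 30 v 30, d = 1**

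| Reading | Two-sided | One-sided |
|---|---|---|
| Exact t, factor 200 | 49.5% | 57.6% |
| Normal approximation, factor 200 | 58.3% | 65.3% |
| Pooled error df of a 4 × 30 model, factor 200 | 53.9% | 61.5% |
| Exact t, no correction | 96.8% | 98.6% |

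None of these gives 80%.

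**What would give 80%**

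- At 30 v 30 and alpha .00025: d of about 1.23 two-sided (1.18 one-sided).
- At 60 v 30 and alpha .00025: d of about 1.05 two-sided.
- At d = 1 with equal groups: 44 per group two-sided (43 gives 78.5%), or 41 one-sided.
- At d = 1 and 30 v 30: a Bonferroni factor of about 13 two-sided, or 26 one-sided.

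**The case against.** **Power at one voxel is not power for the region.** This is the strongest objection. Under voxelwise Bonferroni, a region counts as positive if any voxel survives, so the 200-fold penalty comes with up to 200 chances to detect. A simulation of 30 v 30 at two-sided alpha .00025 shows the possible gain. It assumes d = 1 at each active voxel and equal correlation between voxels; the plan gives neither.

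| Between-voxel correlation | All 200 voxels active | 20 voxels active |
|---|---|---|
| .70 | about 96% | about 89% |
| .80 | about 92% | about 83% |
| .90 | about 84% | about 74% |
| .95 | about 75% | about 66% |

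This part stands. A reader might infer from the 49.5% that the regional analysis would miss a true d = 1 about half the time. The documents do not support that: the figure holds for a given voxel, or for an effect confined to one voxel. But the table does not rescue the stated 80% either. The plan gives no any-voxel criterion, correlation or extent of effect, and some plausible values still fall short.

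**The test may have been a four-group F-test.** With f = .5 and 4 × 30 at alpha .00025, power is 86%, which would be sufficient. But f = .5 with a span of d = 1 needs two groups at each extreme, a favourable pattern. If one group of 30 differs by d = 1, power is 65%. With the actual sizes (60/30/30/30) and only the comorbid group differing, it is 95%, but that is no longer 30 per group. An omnibus test also does not say which groups differ. The plan names no such test for the imaging data.

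**The main contrasts use 60 comorbid patients.** This stands as a limit on scope. A reader might take 50% as the power of all the baseline comparisons. It applies to the 30 v 30 contrasts only, that is, among the alcohol-only, depression-only and control groups. For comorbid against another group the two-sided shortfall is about 6 points. A one-sided test essentially closes it (79.9%, or 81.6% with error pooled over all 150 participants). But the sentence claims 30 per group and does not mention one-sided testing.

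**d = 1 is a minimum.** Larger effects would give more power. A sample-size claim is still judged at the effect it states, and the plan does not claim 1.23.

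**Multiplicity across paradigms and networks.** A reader might add that the correction covers one region only. How alpha is shared across paradigms, measures and networks is commonly left to the analysis plan, which is not shown, so that is not part of this point.

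**Conclusion.** The point holds as an error in a stated figure. With d = 1, 30 per group and a Bonferroni factor of 200, no two-group test that was tried gives 80%. Per-voxel power is 49.5% two-sided and 57.6% one-sided for 30 v 30, against 73.9% and 79.9% for 60 v 30.

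This rests on two assumptions. One is that the baseline correction factor is 200, which the region size implies and the k = 200 in the same section supports. The other is that the comparison is a two-sample t-test at a voxel. Regional detection could be better or worse than 80%; the documents do not allow it to be calculated. Nor does the error show that the sample is too small for every baseline aim, or that voxelwise inference must be abandoned.

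**What to change.** Correct the Sample size section in one of two ways:

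1. Keep d = 1 and restate the per-voxel, two-sided power as about 50% for 30 v 30 and about 74% for 60 v 30; or
2. Keep 80% power and restate the detectable effect as d of about 1.23 for 30 v 30 and about 1.05 for 60 v 30, saying whether the pilot data support effects of that size.

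In either case, name the group-level test, its sidedness, the number of tests corrected for, and what counts as detection (a given voxel, or any voxel in the region). If the any-voxel criterion is meant, state the assumed spatial correlation and extent of effect and give the power from a simulation.

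As an option, the sponsor could make the confirmatory test a single test on the mean signal of a pre-named region and restate the power for it. If d = 1 holds for the regional mean, two-sided power at alpha .025 is 93.9% for 30 v 30 and 98.5% for 60 v 30. The price is that the confirmatory claim no longer localises the effect within the region; voxelwise maps could stay as secondary results. This is a design choice and is not needed to correct the error.

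The correction costs a few sentences and no extra patients.

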### Randomization

After completion of baseline assessment, comorbid patients will be randomly assigned to one of the two group interventions. To reduce the time between the initial study recruitment and the start of the group therapy, the randomization order will be determined with a block randomization with 6 participants per block for each treatment arm. Randomization will be performed by a researcher who is not involved in the recruitment, using a computerized randomization tool implemented in MATLAB (The MathWorks Inc., Natick, Massachusetts, United States). Participants will be recruited and enrolled by trained research staff; the allocation sequence will be concealed from them. Since the study offers psychotherapeutic interventions, patients are not blinded to their intervention arms.

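### The stated 80% power for the BAT-versus-MBT group x time test cannot be reproduced from its own inputs, which give about 46% (N = 54) to 54% (N = 60)

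*Protocol article*

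**What the plan says.** The Participants section plans for "Sixty comorbid alcohol dependent and depressed patients". Under Sample size, these patients are to be "randomly assigned to one of two group therapy interventions" and scanned a second time. The power statement is made "assuming a small to medium effect size (*f* = .2) for the group x time interaction". The two scans of one patient are taken to have a correlation of .7. The section then claims that "we achieve a power of 80% to detect differences", with the .05 level Bonferroni corrected for a region of interest of k = 200, and that this holds "even when we have to face a drop-out rate of 10" per cent. Earlier in the same paragraph the regions are described as having 200 voxels, and G*Power 3.1 is named as the software.

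The next sentence begins "While we expect an attrition rate of 20" per cent. It goes on to say that recruitment will continue, and drop-outs be replaced, until the desired sample sizes are reached.

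**The concern.** The paragraph gives an effect size, a correlation, a correction, a drop-out rate and a resulting power, so the result can be checked directly. A Bonferroni correction over 200 voxels is severe, and 54 patients in two arms looked too few to carry it.

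BAT versus MBT is the only randomised comparison in the trial, and neural activation and connectivity are its primary outcomes. The Additional information section commits to publishing even if the intervention proves to have no influence on the brain measures. A reader of such a null result would rely on the stated 80%. If the true figure is near 50%, the null says much less than the power statement suggests.

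**Working it through.** **Inputs**
- Randomised N = 60 (Participants). After 10% drop-out (Sample size), N = 60 × 0.9 = 54. With all drop-outs replaced, N = 60.
- Two arms. Equal allocation is an inference from "block randomization with 6 participants per block for each treatment arm" (Randomization); no ratio is stated.
- m = 2 fMRI sessions, T1 and T2 (Study procedure; Table 1).
- f = .2, r = .7 (Sample size).
- alpha = .05/200 = .00025, reading k = 200 as 200 voxels.

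**Formula.** This is the G*Power default for the within-between interaction in a repeated-measures ANOVA. The stated r enters only under this effect-size option:

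lambda = f² × N × m / (1 − r), with F on 1 and N − 2 degrees of freedom.

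**Attempt to reproduce the 80%**
- N = 54: lambda = .04 × 54 × 2 / .3 = 14.4. Critical F(1, 52) at .00025 is 15.46. Power = 45.6%. A simulation of 200,000 trials, using a t test on change scores, gave 45.7%.
- N = 60: lambda = .04 × 60 × 2 / .3 = 16.0. Power = 54.3%.

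**Other readings at alpha = .00025**

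| Reading | N = 54 | N = 60 |
|---|---|---|
| Two-sided, as above | 45.6% | 54.3% |
| One-sided | 53.7% | 62.2% |
| Normal approximation, two-sided | 55.3% | 63.2% |
| Three time points (not the fMRI schedule) | 69.5% | 77.8% |
| Other G*Power effect-size options | about 1% | about 1% |

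None reaches 80%.

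**What would give 80%**
- At N = 54, alpha of about .005 gives 80.04%. Since .05/.005 = 10, that is a correction for about 10 tests.
- With no correction (alpha = .05), N = 54 gives 96.1%, so the stated figure is not the uncorrected power either.
- At alpha = .00025 and N = 54, 80% would need f of about .254 or r of about .81.
- With f and r as stated, 80% at alpha = .00025 needs about 84 analysed patients.

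**What f = .2 means here.** In a 2 × 2 layout the interaction moves each cell mean by ± f × SD, so the arms' mean changes differ by 4 × .2 = 0.8 single-session SD. The SD of a change score is √(2 × (1 − .7)) = √.6 = .775 single-session SD. Hence d = 0.8 / .775 = 1.03 on the change score. Check with 27 per arm: 1.033² × 27 / 2 = 14.4, the same lambda.

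For comparison, take d = 0.4 on the change score as an assumed smaller difference. At N = 54 its power is 30% at uncorrected .05 and about 1% at .00025.

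**The case against.** **The number of tests.** The strongest defence is that no corrected alpha is printed. The images are smoothed, so neighbouring voxels are correlated, and the authors may have used fewer effective tests. The baseline claim in the same paragraph (d = 1, 30 per group, 80%) behaves similarly: a two-sample t test gives 49.5% at .00025 and 82.5% at .005. This is a plausible account of where 80% came from, and it is why the finding is that the figure cannot be reproduced as written. It does not rescue the text, which names Bonferroni and 200 and gives no other number.

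**Attrition.** A reader might infer from the expected 20% attrition that the analysed sample is 48, with power of 36.6%. The documents do not support this, because the same sentence provides for replacing drop-outs until the target is met. The 10% reads as a stated margin of safety, and N = 60 is the plan's own case.

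**The effect label.** A reader might also infer that calling f = .2 small to medium is a mistake. On the conventional f scale (.10 small, .25 medium) the label is fair. The difference becomes large only when expressed as change, because r = .7 shrinks the SD of change. This calls for clarification and is not an error.

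**Exploratory purpose.** The Aim section says the intervention effects will be explored, and the Discussion says the study was not designed to evaluate treatment effects per se. No passage plans to read a null as equivalence. That limits the consequence, but the 80% is claimed for the neural effect itself.

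**Conclusion.** The concern holds as a failed calculation. On the stated inputs, power for the group x time test is about 46% at N = 54 and about 54% at N = 60, against the stated 80%. The shortfall is roughly 26 to 34 percentage points, and full replacement of drop-outs does not close it.

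The result assumes that k = 200 means a plain Bonferroni division over 200 voxels, equal arms, two scans per patient and a two-sided test. Only the first could restore 80%, and then only with about 10 tests at N = 54, which the document does not state. If that was the calculation, the correction is what is misreported.

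The conclusion does not extend to a claim that the trial is too small for its purpose, nor to the lower power at N = 48.

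**What to change.** In the Sample size section, do one of the following:
- Keep the 200-voxel Bonferroni correction and restate the power as about 46% at N = 54 and about 54% at N = 60.
- If a smaller effective number of tests was used, state that number and the corrected alpha, recompute the power from them, and make the analysis use the same correction.

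In either case, add beside f = .2 that with r = .7 it corresponds to a between-arm difference in change of 0.8 single-session SD (d about 1.03 on the change score). This keeps the power from being read as covering small differences in change.

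Testing the mean signal of a pre-specified region is an optional alternative. It would change the analysis, and its power would have to be recomputed for the regions, paradigms and measures actually tested; f = .2 cannot simply be carried over from a voxel to a regional mean.

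The first two changes need no extra patients. Restating the power is a change of wording; naming a different correction also binds the analysis to it. The downside of restating is a less favourable published power.

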### Sample recruitment

Participants of the study are recruited by means of several sources in the community around Mannheim, Germany. These include advertisement in local newspapers, announcements on our institutes’ homepage, flyers in local businesses and university campuses; and contact with potential referral sources, for example general practitioners, private psychologists and psychiatrists, as well as local psychiatric inpatient and outpatient units.

Prospective participants express their interest to the research team through email or phone call. After carefully informing the participants about the aim, content, duration and potential risks and benefits of the study, trained research assistants assess initial eligibility using a specifically developed telephone screening. In case the participants are currently in one of the local inpatient or outpatient facilities of the institute, participants will be personally approached and screened. If the individual meets the inclusion criteria, they receive a letter including a detailed study description, the informed consent, time and date of their study appointment and an online link with questionnaires.

### Study procedure

Before participants will be finally included in the study, any open questions, risks and benefits will be discussed with a trained psychologist at the T1 assessment. On agreement of the participant, the informed consent form will be signed and a copy handed to the participant. Afterwards, participants will undergo a psychological interview assessing previously received therapy, current medication and for patients symptoms of depression or alcohol use disorder according to DSM-5. Before the fMRI measurement starts, all paradigms are explained to the participant. Also before and after the fMRI session, participants are asked to fill out questionnaires regarding their current mood and craving. Only comorbid alcohol dependent and depressed patients will be randomized to either receive BAT or MBT group training for 6 weeks. For comorbid patients, the fMRI procedure followed at T1 will be repeated at T2. Afterwards, comorbid patients will be contacted after three months for a catamnestic exploration. All participants will be compensated for their time with 15€ per scanning session plus the money won in the reward paradigm. To promote participant retention and complete follow-up we will contact the comorbid patients by phone during the follow-up period.

### Randomization

After completion of baseline assessment, comorbid patients will be randomly assigned to one of the two group interventions. To reduce the time between the initial study recruitment and the start of the group therapy, the randomization order will be determined with a block randomization with 6 participants per block for each treatment arm. Randomization will be performed by a researcher who is not involved in the recruitment, using a computerized randomization tool implemented in MATLAB (The MathWorks Inc., Natick, Massachusetts, United States). Participants will be recruited and enrolled by trained research staff; the allocation sequence will be concealed from them. Since the study offers psychotherapeutic interventions, patients are not blinded to their intervention arms.

### Psychotherapeutic Interventions

Comorbid patients will be randomly assigned to one of two group therapies consisting of 6 participants. Both interventions consist of six sessions of 2 h therapy with 1 session per week offered by a psychotherapist. To increase adherence, ﻿each participant will receive an individual therapy session before the group therapy begins. The group therapy protocols in both arms are manualized and supervised by an experienced psychotherapist to ensure protocol adherence. Patients who missed more than one session or experienced a severe relapse during the intervention period will be excluded from the protocol. In the unexpected case of an adverse event or harm during the psychotherapeutic intervention (for example, severe aggravation like suicidality), the affected patient will also be excluded and additional in- or outpatient treatment will be offered by the psychotherapist.

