### Secondary outcome measures

Secondary outcome measures include craving and depression scores, as well as relapse rates.

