### Data analyses plan

Analyses will be conducted on an intention to treat and treatment completers principle.

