### Behavioral data analyses

Analysis will be completed by using (repeated measures) analysis of variance (AN(C)OVA) in order to test group differences (AUD vs MD vs Co vs HC) and treatment groups (BAT vs MBT). Difference scores will be calculated. All measures will be compared between groups, as well as treatment groups and interaction effects will be explored. Wherever appropriate, missing data will be imputed using multiple imputation.

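### Excluding randomised patients after missed sessions, severe relapse or adverse events, and replacing drop-outs, conflicts with the promised intention-to-treat analysis and puts the relapse outcome at risk

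*Protocol article*

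**What the plan says.** All references are to the protocol article.

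- **Randomization:** comorbid patients are allocated to behavioral activation (BAT) or mindfulness-based therapy (MBT) once baseline is complete. Anything that happens during the six weeks of therapy is therefore post-randomisation.
- **Psychotherapeutic Interventions:** "Patients who missed more than one session or experienced a severe relapse during the intervention period will be excluded from the protocol". After an adverse event or harm, "the affected patient will also be excluded and additional in- or outpatient treatment will be offered by the psychotherapist".
- **Sample size:** the power statement allows for 10% drop-out, but 20% attrition is expected, and "recruitment will be continued until the desired sample sizes are reached and drop-outs will be replaced by new participants".
- **Data analyses plan:** "Analyses will be conducted on an intention to treat and treatment completers principle".
- **Behavioral data analyses:** "Wherever appropriate, missing data will be imputed using multiple imputation". The fMRI analysis sections describe no counterpart for missing T2 scans.
- **Secondary outcome measures:** "Secondary outcome measures include craving and depression scores, as well as relapse rates".
- **Study procedure:** comorbid patients are contacted after three months and phoned during follow-up. Excluded patients are not mentioned either way.
- **Table 1:** the Form 90 alcohol-use interview is scheduled at T1 and T3 only.

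**The concern.** All three grounds for exclusion (attendance, severe relapse, adverse events) arise after allocation, and the assigned therapy can influence each of them. If patients who meet them leave data collection and are replaced, the patients left in each arm are those who tolerated and attended that arm's therapy without severe relapse. The BAT versus MBT comparison then loses the protection of randomisation whenever the arms differ on those events. That applies to T2 brain change, which is the primary outcome in the randomised part, as well as to craving, depression and relapse.

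Relapse has an additional problem, because severe relapse is both a reason for removal and an instance of the outcome being counted.

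This is more than detail an article may leave to an analysis plan. Exclusion and replacement decide which data are collected, and a later plan cannot recover data that were never collected.

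**Working it through.** **1. The rules side by side.** Randomise, then exclude on events during therapy, then replace drop-outs until the target is reached. Followed literally, this ends with about the target number of completers. An intention-to-treat analysis needs every randomised patient in the assigned arm, with outcomes sought for all. The article leaves four things unstated:
- whether excluded patients still have T2 and T3;
- whether they stay in the intention-to-treat set;
- whether they are the drop-outs who are replaced;
- whether an excluding relapse counts in the relapse rate.

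**2. The plan's own figures.** The article gives no number for exclusions, only the 20% expected attrition and the 10% in the power statement. The 80% power stated for the group-by-time interaction was checked with N = 60 × 0.9 = 54, f = 0.2, correlation 0.7 and alpha = 0.05/200 = 0.00025. The noncentrality is N·f²·m/(1 − ρ) = 54 × 0.04 × 2/0.3 = 14.4 on 1 and 52 degrees of freedom. Power is 45.6% (96.1% at alpha 0.05), so the 80% does not reproduce. That is a separate matter, and nothing below depends on it.

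**3. How many patients are affected.** Inputs are 60 comorbid patients (Participants) and 20% attrition (Sample size). It is an assumption that all attrition falls after randomisation and that the target means 60 retained.
- Randomised = 60/(1 − 0.20) = 75, so 75 − 60 = 15 lie outside the retained sample.
- At 10%: 60/0.90 = 66.7, so 67 randomised and 7 outside.
- Without replacement, 60 randomised leave 60 × 0.80 = 48 or 60 × 0.90 = 54.

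**4. Relapse, as an illustration.** Let r be severe relapse during therapy and q later relapse among the rest. The article gives neither, so both are assumed.
- All randomised: r + (1 − r)q.
- Retained patients only: q.
- Understatement: r(1 − q).

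Take 25% to 100% of the 20% attrition to be severe relapse (r = 0.05 to 0.20), and q = 0.20 or 0.40:

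| r | q | all randomised | retained only | gap |
|---|---|---|---|---|
| 0.05 | 0.20 | 24% | 20% | 4 points |
| 0.05 | 0.40 | 43% | 40% | 3 points |
| 0.20 | 0.20 | 36% | 20% | 16 points |
| 0.20 | 0.40 | 52% | 40% | 12 points |

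The gap is 3 to 16 points if only retained patients are counted.

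**5. Difference between arms, also assumed.** With r = 20% v 10% and q = 25% in both arms, the rates among all randomised are 0.20 + 0.80 × 0.25 = 40% and 0.10 + 0.90 × 0.25 = 32.5%. Retained patients show 25% v 25%. The vanishing of the 7.5-point difference follows from setting q equal in the arms. It shows the mechanism and does not predict a result.

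**The case against.** The strongest reply is that the article can be read consistently. It names both an intention-to-treat and a completer analysis, which would have little purpose if excluded patients left every data set. The exclusion sentence stands in the therapy section, shortly after the word protocol is used for the group-therapy manual, so it may mean removal from the group only. The three-month contact is described for comorbid patients without exception, and multiple imputation is available for behavioral data. A relapse that triggers exclusion is known to the team and can be counted. Continued recruitment is compatible with adding patients to the randomised total.

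Much of this stands. A reader might infer that intention to treat cannot be done, that excluded patients have no T2 or T3 data, or that relapse is understated in every analysis. The documents do not support these: the first two go beyond the text, and the third is certain only for completers. It is likewise an inference that excluded patients are the drop-outs who are replaced. The lack of a ranking between the two analysis sets is something an article may leave to the analysis plan, and is not a fault here.

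Two further replies limit the scope. The four-group T1 comparison, which serves the primary aim, is untouched. The Discussion says the study was not designed to evaluate treatment effects per se, and some T2 scans will be missing after relapse under any wording because abstinence is required for scanning. Even so, the article calls itself a randomised-controlled trial, compares BAT with MBT and promises intention to treat. The favourable reading is possible, but nothing in the text secures it.

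**Conclusion.** The exclusion and replacement rules conflict, on a plain reading, with the declared intention-to-treat analysis, and the passages must be reconciled. Up to about 15 of about 75 randomised patients are affected, if all of the expected 20% attrition falls after randomisation and 60 retained patients is the target. The article does not say when attrition occurs or why, so 15 is an upper figure.

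For completers, severe relapse during therapy is zero by construction. For intention to treat, the loss is conditional on excluded patients not being followed or their known relapse not being counted. The 3 to 16 points are illustrative, not estimates. The exposure is greatest for the T2 scan, where no imputation is described, and for alcohol use, where a patient not followed to T3 has no scheduled Form 90 after baseline. The matter should be settled before such data are lost.

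**What to change.** Reconcile the Sample size, Psychotherapeutic Interventions and Data analyses plan sections by separating the end of group therapy from the end of study follow-up. This neither changes nor judges the clinical rules. State that:

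1. All randomised patients remain in the intention-to-treat set in the arm assigned.
2. T2 questionnaires, the T2 scan where scan criteria are met, and the T3 contact continue where consent and safety allow.
3. A severe relapse that leads to exclusion counts as an event in the relapse outcome.
4. Replacement recruits add to the randomised total and displace no one.
5. The completer analysis is read as supportive.

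The cost is a change of wording and follow-up of up to about 15 more patients. Some T2 scans will still be missing after relapse, and the treatment contrast will be somewhat diluted because patients with incomplete therapy are included.
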